### 8.1 Primary study parameter(s)

Our primary study parameter is the incidence of delirium. Delirium is screened with the DOS score. DOSS is a shortened version with 13 items and is scored three times a day. A delirium is highly presumable if the patient had a DOSS of  $\geq 3$  and scored three times in a row. When delirium is suspected a geriatrician will be consulted to confirm the diagnosis using the DSM-IV criteria. We will describe the severity of the delirium using the DOS score (13 points is maximum). Also duration of delirium will be measured in days.

### 8.2 Secondary study parameter(s)

Secondary we will measure mortality within one year after surgery. Also duration of hospital stay, ICU admission, and complications during hospital stay will be investigated.

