## 1. INTRODUCTION AND RATIONALE

The population of people above 65 years old is expected to double in the next 35 years. The increase of age is associated with an increase in need for medical care and number of patients requiring surgery. A higher rate of post-operative complications, like a delirium (37%), longer hospital stay, ICU admission, and mortality is associated with increasing age.[1, 2]

In our hospital, within the population of 70 years or older, approximately 85 patients per year undergo surgery for colorectal cancer and about 50 patients per year undergo surgery for abdominal aortic aneurysm. We expect an increase in the number these surgical procedures performed during the coming years (also due to the implementation of screening programs).

A delirium is often a fatal disorder. It affects as much as 50 % of the elderly people who are hospitalised. In the population described above, the incidence of a delirium is about 15%. The 6-month mortality is increased within patients with a postoperative delirium (20%) versus no delirium (3%). [3] In short a delirium is a common complication after surgical intervention and results in a significant decrease in quality of life, an increased rate of complications, mortality and additionally is associated with high costs. Therefore a delirium holds essential health relevance.

The cause of a delirium can be the result of a single factor but is mostly a combination of different factors at once. Many factors have been identified and validated to be an independent cause of a delirium. These factors of frailty are for example the patient's nutritional state, physical health, the use of medication, the patient's mental state, laboratory results (such as anaemia and renal function), delirium in patient's history, visual and hearing impairment.

At the moment physicians are already more aware of these frail elderly and these factors of frailty but it is only tackled at admission in hospital or at long care facilities. A delirium is preventable in 30 to 40 % of the cases. Therefore the Hospital Elder Life Program (HELP), a worldwide non –pharmaceutical program, is implemented. This program starts at admission and is proven to be effective to prevent a delirium. [3-5] Another recent study, for patients with an acute hip surgery, shows that specific ortho – geriatric care during admission improves the outcome 4 months after surgery. [6]

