## 2. OBJECTIVES

Our primary aim is to address and tackle the factors of frailty in an early phase, which is possible in elective planned surgery.

We hypothesise that *optimal* preparation, starting 5 weeks before surgery, will reduce the incidence of delirium from 15% to 7,5%. [7]

Our secondary aim is to reduce post-operative complications, hospital stay, and the 6 months mortality compared to a retrospective database made.

We will analyse all pre-, peri -and postoperative factors and the effect on the incidence of delirium, other complications and mortality. This will be done to create a risk model for patients to assess the risk for adverse events post-operatively. Also the costs and cost-effectiveness of this program will be investigated.

In addition we will observe the experience of the first caregiver during the course of illness of the patient. More often direct family and friends are asked to help in the support of patients in need in all forms of care in the Netherlands. First caregivers are asked to actively support the patient in this program. Caregivers are often direct family, partner or children of who their social life and daily activities can be disturbed due to this program.

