#### **Secondary study parameters/endpoints (if applicable)**

Secondary we will measure complication rate, hospital stay, ICU admission, and ICU duration of stay.

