Data about the surgical procedure will be gathered. American Society of Anaesthesiologists' (ASA) classification for physical health is determined before surgery from history and physical examination by the attending anaesthesiologist. Anaesthesia time will be calculated as the duration between tracheal in- and extubation. Also blood loss during surgery and complications during surgery will be noted. All Patients undergoing surgery for colorectal carcinoma or abdominal aortic aneurysm surgery will receive general anaesthesia. Epidural anaesthesia is used as an adjunct as part of the fast track protocol. If patient is not eligible for epidural anaesthesia is not eligible (in case of allergies or coagulopathy), a Patient-Controlled Analgesia pump (PCA-Pump) with Morphine will be used as an alternative. Patients operated on with EVAR will not receive an epidural or a PCA. Other parameters gathered during admission, are complication, ICU stay, transfusion of packed cells, and mortality. Complications are classified using the Clavien –Dindo classification of surgical complications. [22]

At discharge (T3) patients will fill in WHOQOL-Bref, MMSE will be taken, the same blood will be drawn and the CSI will be filled in by first caregiver.

At follow up after six months (T4) and 12 months (T5) WHOQOL-Bref, CSI, MMSE and CESD-16 will be taken. Also function is tested using the TUG test and KATZ – ADL.

Table 2 describes when measurements are repeated to evaluate the effects of the intervention before surgery and after surgery. Laboratory results and physical exercises will be measured at admission.

Addendum describes all questionnaires, patient's chart, and laboratory results.

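### Complications are counted only during the hospital stay, which the programme aims to shorten, so the complication rate can look lower without any complication being prevented

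*Protocol*

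**What the plan says.** Section 8.2 describes the secondary analysis of complications in these words: "Also duration of hospital stay, ICU admission, and complications during hospital stay will be investigated". The data collection matches it. Under OUTO Care in Section 6.2: "Other parameters gathered during admission, are complication, ICU stay, transfusion of packed cells, and mortality". The endpoint list in Section 6.1 gives no window: "Secondary we will measure complication rate, hospital stay, ICU admission, and ICU duration of stay". No part of the protocol sets a fixed number of days after surgery for complications, whereas mortality has fixed horizons of six months and one year.

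Length of stay is a target in its own right. Section 2 states: "Our secondary aim is to reduce post-operative complications, hospital stay, and the 6 months mortality compared to a retrospective database made". The Summary repeats this aim and adds that delirium lengthens the stay.

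On what counts as a complication, OUTO Care says: "Complications are classified using the Clavien –Dindo classification of surgical complications". Section 1 describes delirium this way: "In short a delirium is a common complication after surgical intervention". Section 2, on the risk-factor analysis, refers to "the effect on the incidence of delirium, other complications and mortality". Nothing says whether delirium is inside or outside the complication rate.

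**The concern.** A rate counted from surgery to discharge depends on two things: how often complications occur and how long patients are watched. Here the second is meant to differ between the cohorts. If the programme works as hoped, OUTO patients go home sooner. Complications that would have been recorded late in a longer admission then occur after discharge and drop out of the endpoint, including those that bring the patient back. Because the controls are historical, any drift in discharge practice between the two periods acts in the same way. Section 3 reports no recent major pathway changes, but that cannot cover the programme's own effect on stay.

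At stake is how the complication result is read. A lower OUTO rate would be taken as a benefit when part of it may only reflect shorter observation. If OUTO stays turned out longer, the distortion would run the other way.

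**Working it through.** **The plan's own figure.** The protocol gives no figure for complications. Its sample size supplies the cohort size and the delirium rates used below, and it reproduces: n per group = (1.960 + 0.842)² × (0.15×0.85 + 0.075×0.925) / 0.075² = 7.849 × 0.196875 / 0.005625 = 274.7, that is 275. It is not in dispute.

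**Inputs for the window effect.** The documents give no 30-day complication risk, onset times or length of stay. All three are assumptions here: 30-day risk q of 20, 30 or 40%, identical in both cohorts; control stay of 10 days; OUTO stay of 9, 8 or 7 days.

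**Formula.** The probability of a first complication by day t is F(t) = 1 − exp(−λ(t/30)^k), with λ = −ln(1 − q). Shape k = 1 is a constant hazard; k = 0.5 concentrates events early. The artificial fall is F(10) − F(OUTO stay).

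Example with q = 40% and k = 1: λ = 0.511; F(10) = 1 − 0.6^(10/30) = 15.7%; F(7) = 1 − 0.6^(7/30) = 11.2%; fall 4.4 points (15.66 − 11.24).

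| Hazard | q | Rate at 10 days | Fall if 9 days | Fall if 8 days | Fall if 7 days |
|---|---|---|---|---|---|
| Constant | 20% | 7.2% | 0.7 | 1.4 | 2.1 |
| Constant | 30% | 11.2% | 1.1 | 2.1 | 3.2 |
| Constant | 40% | 15.7% | 1.4 | 2.9 | 4.4 |
| Early | 20% | 12.1% | 0.6 | 1.2 | 1.9 |
| Early | 30% | 18.6% | 0.9 | 1.8 | 2.8 |
| Early | 40% | 25.5% | 1.1 | 2.4 | 3.7 |

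Falls are in percentage points. The range is 0.6 to 4.4.

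**A second set of assumptions.** Take a 35% 30-day risk, exponential onset with mean m days, and a stay of 9 against 7 days. The in-hospital rate is 35% × (1 − exp(−stay/m)) / (1 − exp(−30/m)).
- m = 4: 31.3% against 28.9%, a fall of 2.4 points.
- m = 6: 27.4% against 24.3%, a fall of 3.1 points.
- m = 8: 24.2% against 20.9%, a fall of 3.3 points.

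These lie inside the range above.

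**Limit of both models.** They end observation on a fixed day for everyone. In practice a patient who is becoming unwell is likely to be kept in, so fewer events would fall outside the window and the true artefact would be smaller. With a fixed window of equal length in both cohorts, it is zero by construction.

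**Delirium, conditionally.** If delirium were counted in an any-complication rate, the hypothesised drop from 15% to 7.5% would move that rate by (15 − 7.5) × the share of delirious patients with no other complication. That is 0 to 7.5 points, or 3.75 if the share is one half. The documents do not give the share.

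**The case against.** Four counter-arguments deserve weight.

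*An in-hospital window is a defensible choice with historical controls.* OUTO patients have study visits at 6 and 12 months and adverse-event recording (Sections 6.2 and 7.2), while the controls have record review only (Section 3). Ascertainment after discharge could therefore be fuller in OUTO, and it should not be assumed that missed events are missed equally in both cohorts. This stands. It determines how the fix must be built, but it does not make a window that depends on length of stay neutral.

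*The size is assumed and modest.* This is correct. For the second set of assumptions the standard error of the difference at 275 per cohort is √[(0.313×0.687 + 0.289×0.711)/275] = 3.9 points at m = 4 and, in the same way, 3.6 points at m = 8, so falls of 2.4 and 3.3 points are below one standard error. At the top of the table (15.7% against 11.2%) the standard error is 2.9 points, so 4.4 points is about 1.5 standard errors. A systematic shift of this kind does not shrink with more patients.

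*A reader might infer that delirium is counted a second time inside the complication rate.* The documents do not establish this. The description of delirium as a complication is background text in Section 1. Where outcomes are listed (Summary, end of Section 1, Section 2, Section 6.7), delirium and complications appear as separate items. A fall in delirium would also be a real fall. What remains is that the rate's content is not stated.

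*A reader might infer that post-discharge complications are not captured at all, or that the Section 6.7 comparison is confined to the admission.* Neither is supported. Adverse events are recorded throughout, complication information is kept for withdrawn patients (Section 6.6), and Section 6.7 gives no window for its complication rate. The restriction applies to the Section 8.2 endpoint and the data collection that feeds it.

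**Conclusion.** The point holds for the observation window. The protocol confines the secondary complication endpoint to the admission while aiming to shorten the admission, so the cohorts may be observed for different lengths of time and the rate can favour the one discharged earlier. The size cannot be obtained from the documents. Under the assumed risks, onset patterns and stays it is roughly 0.6 to 4.4 percentage points, smaller if complications prolong stay, and nil if stay does not change.

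On delirium, the conclusion is only that the protocol should say whether it enters the rate. It does not show that the primary endpoint is double counted. The primary analysis and sample size are untouched. This should be corrected, but it concerns one secondary endpoint.

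**What to change.** - Define the secondary complication endpoint in Sections 6.1 and 8.2 as Clavien-Dindo complications within a fixed window after surgery, for example 30 days, including readmissions to the hospital.
- Ascertain it in both cohorts from the electronic record alone. Use routine clinical entries, and do not use OUTO study visits, the OUTO study folder or adverse-event reports.
- Keep the in-hospital rate as a supportive result.
- State the same window for the complication-rate comparison in Section 6.7.
- Report the rate excluding delirium, with the rate including it as supportive.

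The cost is a change of wording and slightly more chart review in both cohorts, with no new visit. The downside is that post-discharge events treated elsewhere may be missed, possibly not equally in the two cohorts. The report should say so.

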### 8.3 Other study parameters

All factors of frailty will be evaluated and analysis will be done to confirm association with the incidence of delirium.

### 8.4 Interim analysis (if applicable)

Interim analysis is not possible, because at that point, not enough patients will be gathered to obtain any significant value.

## **9 ETHICAL CONSIDERATIONS**

### **9.1 Regulation statement**

The study will be conducted according to the principles of the Declaration of Helsinki 64th WMA General Assembly, Fortaleza, Brazil, October 2013 and in accordance with the Medical Research Involving Human Subjects Act (WMO) and other guidelines, regulations and Acts.

### **9.2 Recruitment and consent**

Patients are recruited during multidisciplinary meeting. Within three days patients will be informed by their doctor (gastroenterologist or vascular surgeon) to explain the agreement made during this multidisciplinary meeting. Also they will give written and spoken information, including the informed consent form.

If patient gives spoken approval to their physician, the researcher will contact the patient to give spoken explanation about the study and to plan the 70PLUS outpatient clinic appointment. During this appointment informed consent will be obtained and the informed consent form will be signed. The patient will receive a copy of the signed informed consent form.

### **9.3 Benefits and risks assessment, group relatedness**

The burden of this study consists mostly of the visit to the outpatient clinic and several questionnaires taken.

Probable risks to the subject consist only of drawing blood, physical exercises and if anaemic i.v. iron injection. We expect a minimal risk for adverse events due to these actions. All will be done by experienced personnel.

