### 3. STUDY DESIGN

This study will be a prospective interventional study, starting 1 January 2016, and planned until 31 December 2017.

A pre-operative clinical pathway is set up for patients of seventy years or older with surgical indication for colorectal cancer or abdominal aortic aneurysm, the 70 PLUS outpatient clinic in our surgery department. Within one week since indication for surgery is decided, a nurse practitioner, a physiotherapist and a dietician will see these patients and all factors of frailty will be investigated. If needed, a geriatrician will also see the patient for complete geriatric assessment and advice during admission to prevent delirium (criteria for CGA is described in *chapter 6.2 study procedures*). Diet advice and physical exercises will be given to all patients in need. Patients must follow these advices and keep a diary.

All patients aged  $\geq 70$  years will be included in this study to follow our pre-operative clinical pathway for optimisation. Also patients, who are not clinically fit to wait for 5 weeks will be included and optimised until surgery.

We propose an optimum preparation time during 5 to 6 weeks till surgery. This is based on the SONCOS quality guidelines 2015 for colorectal cancer, in which a maximum delay of 6 weeks is proposed from pathology result until surgery (Addendum: SONCOS quality guidelines 2015 for colorectal cancer ).

Prospectively gathered data of all cases will be compared to a retrospective, historical, control group of comparable patients from 1 March 2013 till 1 March 2015.

These patients have not been evaluated for factors of frailty in advance. This is a cohort of patients of the age  $\geq 70$  years who received treatment for colorectal cancer with or without neo-adjuvant therapy (radiation or chemotherapy). Both open and laparoscopic surgery will be included.

Also patient who received treatment for abdominal aneurysm of the age  $\geq 70$  are included. These patients underwent an EVAR or open repair. (Complete description of the pathway in the retrospective group is described in *chapter 6.2 Study procedure* and addendum *Amphia protocol Colonchirurgie*)

Only electively planned surgery is included, all emergent or urgent surgical procedures are excluded.

Data of patients in both groups will be gathered in the Amphia Hospital Breda, the Netherlands.

All information will be gathered using Hyperspace Version IU4 (Epic, Inc., Verona, WI).

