## 5. TREATMENT OF SUBJECTS

This prospective study is set up as an outpatient clinical pathway in which we intend to intervene in the usual pathway until operation. Within one week after setting indication for surgery, patients will be assessed. A nurse practitioner, a dietician and a physiotherapist will see the patients and if necessary a geriatrician will be involved (specific criteria for consulting dietician or geriatrician are defined in chapter 6.2 *Study procedures*).

In the usual pathway, patients are seen by the surgeon and are planned for surgery as soon as possible (which is the case in the retrospective group).

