### Investigational product/treatment

Laboratory results to evaluate haemoglobin for intravenous iron (IVI), electrolytes for suppletion and nutritional status for refeeding.

Dietician's advice or refeeding products in patients with malnutrition.

Physical exercise for all patients and keeping a daily diary.

In case a geriatrician is consulted, they will assess if preventive interventions for delirium are needed (e.g. starting haloperidol).

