#### **Serious adverse events (SAEs)**

A serious adverse event is any untoward medical occurrence or effect that

- results in death;
- is life threatening (at the time of the event);
- requires hospitalisation or prolongation of existing inpatients' hospitalisation;
- results in persistent or significant disability or incapacity;
- is a congenital anomaly or birth defect; or
- any other important medical event that did not result in any of the outcomes listed above due to medical or surgical intervention but could have been based upon appropriate judgement by the investigator.

An elective hospital admission will not be considered as a serious adverse event.

The use of i.v. iron injection, can cause allergic reaction. This product is used normally for all anaemic patients with iron deficiency with specific surgical indication. In-hospital protocol is already in use. No other or extra care will be undertaken. Addendum describes the in-hospital protocol for the use of i.v. iron injection (in Dutch).

Due to physical exercises patient can have muscle complaints, or even fall. Usual care will be given.

All events will be reported by the investigator (CM) to the sponsor (LLA). Patient will still be included in our database and will not be withdrawn from this study when an adverse event occurs.

To our knowledge no other adverse events might occur when participating in this study.

The investigator will report all SAEs to the sponsor without undue delay after obtaining knowledge of the events, without any exceptions except for the following SAE:

- If death occurs during this study due to the normal cause of illness, we will not notify this as a SAE.

The sponsor (LLA) will report the SAEs through the web portal *ToetsingOnline* to the accredited METC that approved the protocol, within 7 days of first knowledge for SAEs that result in death or are life threatening followed by a period of maximum of 8 days to complete the initial preliminary report. All other SAEs will be reported within a period of maximum 15 days after the sponsor has first knowledge of the serious adverse events.

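### The closed risk list omits the longer preparation interval and possible haloperidol, and an undefined exemption could leave pre-operative disease deaths unnotified as SAEs

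*Protocol*

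**What the plan says.** **Risk text.** Section 9.3 tells the ethics committee that "Probable risks to the subject consist only of drawing blood, physical exercises and if anaemic i.v. iron injection". Section 7.2, under serious adverse events, mentions an allergic reaction to iron, muscle complaints and falls, and then closes the list: "To our knowledge no other adverse events might occur when participating in this study".

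**Pathway text.** Section 5 describes usual care, which the retrospective group received: "patients are seen by the surgeon and are planned for surgery as soon as possible". For the study pathway, section 3 says "We propose an optimum preparation time during 5 to 6 weeks till surgery". It gives one basis for this interval: "This is based on the SONCOS quality guidelines 2015 for colorectal cancer, in which a maximum delay of 6 weeks is proposed". Under the investigational treatment heading of section 5, the protocol says of the geriatrician that "they will assess if preventive interventions for delirium are needed (e.g. starting haloperidol", and section 6.2 (OUTO Care) names haloperidol again.

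**Reporting of deaths.** Section 7.2 puts death first among its SAE criteria and requires prompt reporting of all SAEs, with one exception: "If death occurs during this study due to the normal cause of illness, we will not notify this as a SAE". It does not say what counts as such a death or who decides.

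**Mortality endpoint.** Section 8.2 starts the one-year mortality count at surgery. The Summary and section 6.7 speak of six-month mortality and name no starting point. The wording of section 6.1 on one-year mortality can be read either way.

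**The concern.** Section 9.3 says that the risks consist *only* of three items. That makes it a positive statement about the whole programme, not a summary that leaves detail to another document. Two elements of the programme are outside it: a planned interval before surgery that differs from usual care, and a possible preventive drug.

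The exemption for deaths compounds this. The illness being treated is the one whose operation is scheduled after the preparation period. A death from that illness before the operation is the event for which one would most want to ask whether the study's timing played a part. It is also an event that fits the wording of the exemption. If mortality is counted from surgery, the same death may be missing from the endpoint as well. At stake is whether the sponsor and the ethics committee would be notified of such a death promptly, and whether the final report would show it.

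**Working it through.** The point rests on no calculated figure in the protocol, so the check is a comparison of texts, with one small piece of arithmetic on the population concerned.

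1. **Risk list against pathway.** Items named as risks or foreseen events in sections 7.2 and 9.3: blood draws, exercise (muscle complaints, falls) and intravenous iron (allergy). Elements of the pathway in sections 3, 5 and 6.2: assessment and questionnaires, blood draws, dietary advice, exercise, iron if anaemic, geriatric assessment with possible haloperidol, and 5 to 6 weeks of preparation. The last two have no counterpart in the risk text. The first list is worded as complete, so the sections cannot all stand as written.

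2. **Basis for the interval.** The guideline in section 3 is cited for colorectal cancer. No corresponding source is cited for aneurysm. Section 4.1 expects 275 patients, about 20% with an aneurysm: 0.20 × 275 = 55 patients without a cited basis for the interval, and 0.80 × 275 = 220 with one.

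3. **A death between the 70PLUS visit and surgery, followed through the rules.**
 - Section 7.2, definition: it is an SAE, because it results in death.
 - Section 7.2, exemption: if it is attributed to the aneurysm or the cancer, it can be classed as exempt and then not notified. The seven-day report for fatal SAEs would not be made.
 - Section 8.2: it precedes the start of the mortality count and so falls outside that endpoint as worded.
 - Summary, sections 6.1 and 6.7: it may or may not count, because the starting point is not clear.

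4. **A serious but non-fatal event in the same period.** Section 7.2 says that adverse events reported by the patient or seen by staff are recorded, whatever their relation to the study. A life-threatening event or an unplanned admission meets the SAE definition and is not exempt. This route is intact.

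5. **An enrolled patient whose operation becomes urgent.** The exclusion criteria in section 4 apply to potential subjects. The specific withdrawal criteria in section 6.4 do not include this situation, and section 7.2 keeps patients with adverse events in the database. Section 3, however, restricts the study to elective procedures. The protocol does not say how such a patient is counted.

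The gap is therefore narrow: the completeness of the risk list, and the handling of pre-operative deaths attributed to the disease.

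**The case against.** The strongest reply is that nothing is hidden. The preparation interval and haloperidol are stated openly in a protocol that the committee reads in full. The interval is bounded by a guideline maximum for colorectal cancer, and section 3 provides that patients who cannot wait are prepared only until their operation. Haloperidol depends on the geriatrician's judgement, and standard care also allows a geriatrician to visit at admission. Exempting disease-related deaths from SAE notification can be legitimate. Section 6.7 compares complications and six-month mortality with the historical group after one year, and section 6.6 uses complication and mortality data even from withdrawn patients.

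Most of this stands, and it limits the point. It does not remove the contradiction: a bounded or conditional risk is still a risk, and the list is worded as complete. Nor does it define the exemption or settle the mortality start point. Consent pages and addenda are not available here, so nothing is claimed about what patients were told.

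Three stronger readings are tempting, and the documents do not support them.

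- *Events during the wait are invisible.* They are not. Adverse events are recorded and non-fatal SAEs are reportable. Only some deaths may escape notification.
- *A number of missed events can be given.* One could multiply 275 patients by 5 weeks (275 × 5 / 52 = 26.4 patient-years) and apply an event rate. But that is total preparation time for a cohort that all waits five weeks, not added waiting: the usual interval is never quantified, and some patients are operated on sooner. The documents give no event rate for this period.
- *Patients who become urgent are dropped, so the results flatter the programme.* The exclusion criteria govern entry, and no withdrawal rule removes such patients. Exclusion from analysis is possible under section 3 but is nowhere stated.

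**Conclusion.** The point holds in a limited form. Sections 7.2 and 9.3 give a closed list of risks that does not match the pathway in sections 3, 5 and 6.2, and these must be reconciled. Separately, the undefined exemption in section 7.2 could leave a death from the aneurysm or cancer during preparation unnotified, and section 8.2 may leave it outside the mortality endpoint.

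The size cannot be given as a number of events. It can be given only as the population to which the text applies: up to 275 patients, of whom about 55 have an aneurysm and no cited basis for the interval. The conclusion assumes that the exemption is applied as written and that at least some patients wait longer than they would have under usual care, as the contrast between sections 3 and 5 implies. It does not assume that waiting causes harm, and it makes no judgement on the interval or on haloperidol.

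**What to change.** 1. Reconcile sections 7.2 and 9.3 with sections 3, 5 and 6.2, so that the preparation interval and preventive medication appear among the potential risks and the closing statements in 7.2 and 9.3 agree with the pathway.
2. In section 7.2, state that the exemption does not apply to deaths between the 70PLUS visit and surgery. For the deaths it still covers, define the term and say who decides.
3. Give mortality one stated starting point across the Summary and sections 6.1, 6.7 and 8.2.
4. Report descriptively the number of deaths before surgery and the number of operations that become urgent during the wait. Keep the comparison with the historical cohort on the same elective-surgery basis in both groups. That cohort excludes urgent and emergent operations and consists of treated patients, so adding such cases to the OUTO side alone would make the comparison unequal.

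The cost is protocol wording, two extra counts in the report and probably a few more SAE reports. No change to clinical care is proposed.
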